### 2.7. Randomization and Blinding

From all hypertensive patients who had medical records in the Haft-e-Tir comprehensive health services center and were eligible for the study, we will select for the invitation by simple random sampling. Then we will screen them for health literacy stage. After completing the inform consent form, limited health literacy patients will randomly allocate to either the control or the intervention group. Randomization of the participants will be done using permuted block randomization. Due to the nature of this intervention, blinding of the patients to the allocation will not be completely possible.

### 2.8. Outcome Measures

The outcome will be assessed at the baseline, one and 3-month after intervention [Figure 1]. Baseline measurement includes demographic (age, sex, marital status, education, job, income, smoking, and duration of the disease), HBM constructs questionnaire (perceived susceptibility, perceived severity, perceived barriers, perceived benefits, and self-efficacy), and self-care behaviors questionnaire.

### 2.9. Primary Outcome Measures

#### 2.9.1. Self-Care Behavior

Self-care behaviors will be determined using the 31-item hypertension self-care activity level effects (H-scale) prepared by Findlow [28]. This scale aims to help physicians for a better guidance to hypertensive patients who are looking for attaining blood pressure control [29]. The H-scale surveys the level of self-care by questioning about the number of days per week on which an individual carries out a self-care behavior. The H-scale was previously validated in Persian patients with high blood pressure [28]. The Persian version consisted of 27 items that measure the hypertension self-care activities with the following domains: medication adherence (3 items), physical activity (2 items), low-salt diet (10 items), smoking (2 items), alcohol (1 item), and weight management (9 items). The Persian version of the scale shows adequate internal consistency. Cronbach alphas were as follows: medication adherence (Cronbach's *α* = 0.91), low-salt diet (Cronbach's *α* = 0.72), physical activity (Cronbach's *α* = 0.96), smoking (Cronbach's *α*= 0.91), and weight management (Cronbach's *α* = 0.85).

### 2.10. Secondary Outcome

#### 2.10.1. Knowledge of Hypertension

 Hypertension knowledge will be assess by using Hypertension Knowledge Level Scale (HK-LS); this 22-item scale is prepared by Erkoc et al. [30]. Hypertension Knowledge Level Scale (HK-LS) will assess respondents' knowledge in defining hypertension, lifestyle, medical treatment, drug compliance, diet, and complications of hypertension. Each item is a full sentence that is either correct or incorrect. And each item is prepared as part of a standard answer (correct, incorrect, or do not know). Motlagh et al. have validated this questionnaire in Iranian population [28]. In Persian version in the validation process, two items were excluded from the scale and the final version has 19 true/false items.

#### 2.10.2. Health Belief Model Constructs

In order to assess the constructs of health belief model, a researcher made the questionnaire that will be used. Items developed for susceptibility, seriousness, benefits, barriers, and self-efficacy focused on self-care behaviors in hypertensive patients. 39 items with 5-point Likert answers will be used. Nine items for perceived benefits, 7 items for perceived barriers, 9 items for perceived susceptibility, 6 items for perceived severity, and 10 items for perceived self-efficacy were written. For determination of content validity, the list items were distributed to judges who were faculty members and PhD candidates and they were quite familiar with HBM constructs. In content validity, altering the format of questions and ignoring irrelevant questions were done. Then, mean Content Validity Index (CVI) and Content Validity Rate (CVR) of the questionnaire were calculated as 0.94 and 0.91, respectively. Reliability of the scale was calculated and the Cronbach's alpha values of knowledge questions were 0.71, 0.70, 0.70, 0.82, and 0.85 for perceived susceptibility, perceived severity, perceived barriers, perceived benefits, and perceived self-efficacy, respectively.

### 2.11. Intervention

#### 2.11.1. Theoretical Framework

HBM constructs are the guidelines for the educational intervention design in this study. In the HBM model, perceived severity, perceived benefits, perceived barriers, and perceived self-efficacy are the determinant components. We will mainly establish the intervention model based on the principal HBM components. Patients randomized to the intervention group will receive four groups of educational sessions (lasting 50-60 min) during four weeks. Topics of the first session are “what is high blood pressure?” and “what is self-care for hypertension?” This session will focus on the strategies to enhance perceived susceptibility and perceived severity of patients toward the disease. In this session, the patients will face the problem (risk of complications of hypertension problems) and they will be threatened (perceived susceptibility). Then, they will understand the depth of the risk and seriousness of complications (perceived severity).

In the second session, patients will learn and discuss healthy diet (such as low salt, low fat, fruit, and vegetable-rich diet). In the third session, patients will learn about physical activity and weight management. The fourth session will focus on medication adherence and avoidance of smoking and alcohol drinking. The importance of self-care behaviors, being physically active, adhering to medication, avoidance of smoking and alcohol drinking, and also possible barriers to a continuous healthy diet, will be discussed. In this session, brainstorming the possible and trained solutions for those barriers will cover the perceived barriers. By discussing the benefits and useful outcomes of adherence to the self-care behaviors, patients will believe the benefits and possibility of their behaviors (perceived benefits). Introducing an appropriate role model (strategy of vicarious experiences [[name]]) in video comics, providing solutions to address possible obstacles in removing the barriers, and giving verbal persuasions to positive expressions of the patients were used to enhance the self-efficacy of individuals for self-care behaviors.

Considering the limited health literacy level of the patients of the study, health literacy strategies will be used in educational material design for enhancing the quality of intervention. In order to cover these strategies, we will use four animated comics and fact sheets with a lot of illustrations and photos which are consistent with the HBM constructs and educational sessions' topics. Animated comics will be produced as media that will be shown to the intervention group patients at the beginning of each educational session to help them start discussing the topic and learn more about the self-care throughout the story of them.

In order to design these animated comics, the research team defines the characters of the story of a hypertensive patient ([name]), her family and friends and also her physician. The story of each part of the comic will cover the topic of the respective educational session. In the scenario of the animated comics we will make some recommendations for self-care behaviors to hypertensive patients. In the next step, the research team will design the storyboard of each part of the animated comic and then the characters and backgrounds will be illustrated compatible with the culture of the patients of the study using Adobe Illustrator software by a graphic designer. At last, the sounding and animating of each part of the storyboard will be done using Adobe After Effect software by an animation team.

The fact sheets that contain the most important recommendations and reminders of the educational topic will be designed based on existing standards and guidelines for designing simple and comprehensible educational media for limited health literacy patients, such as Simply-Put [31], which is provided by the Center for Disease Prevention and Control as a comprehensive guide for designing simple, understandable media. For optimal comprehension and compliance, it is suggested that patients' educational materials will be written at a sixth-grade or lower reading level, preferably including pictures and illustrations [32]. Therefore, Gunning Fog Index will be used to assess the readability of these written materials. This formula determines how difficult it is to read and understand a piece of writing. Readability will be calculated by the following formula: GFI = [(number of words/number of sentences) + number of “difficult words”] x 0.4 [33]. The number that results from the following calculation correlates with the grade level. All the sentences will design and modify in such a way that based on this indicator, scores less than 6 will be obtained for the readability level [32]. Each designed fact sheet will be given to the intervention group patients at the end of each educational session.

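### The fact-sheet readability formula adds an undivided count of difficult words to average sentence length, so the fixed cut-off of 6 changes meaning with the length of text scored

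*Protocol article*

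**What the plan says.** Section 2.11.1 (Theoretical Framework) of the protocol article describes the written fact sheets handed out at the end of each of the four sessions. It cites a suggestion that "educational materials will be written at a sixth-grade or lower reading level", and on that basis says the "Gunning Fog Index will be used to assess the readability of these written materials".

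The formula follows: "Readability will be calculated by the following formula: GFI = [(number of words/number of sentences) + number of" difficult words, with the whole bracket multiplied by 0.4 and reference [33] cited. Two statements say what the score means: "This formula determines how difficult it is to read and understand a piece of writing", and "The number that results from the following calculation correlates with the grade level".

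The section then sets a pass rule. Sentences are to be written and revised so that "scores less than 6 will be obtained for the readability level". It gives no division by total words, no percentage and no fixed sample length for the difficult-word term, and does not say whether a sheet, a sample or a sentence is scored.

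**The concern.** The two terms in the bracket behave differently. Words divided by sentences is an average, so it stays the same if a text is printed twice. A count of difficult words doubles. The score therefore rises although the text is no harder to read, which conflicts with the section's own account of the score as a measure of difficulty that goes with grade level.

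This is more than a background remark, because the formula and the cut-off together are the only numerical criterion given for the fact sheets, and the participants are selected for limited health literacy. Under the printed rule, two sheets of equal difficulty can fall on opposite sides of the cut-off because one is longer, and a short sheet dense in hard words can pass. The article also does not leave the formula to a fuller document. It prints it, so anyone reusing the materials would inherit it.

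**Working it through.** **Inputs from Section 2.11.1.** The printed formula, the multiplier 0.4, and the pass rule of below 6. The plan reports no computed score, so there is no figure to reproduce.

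**Inputs assumed.** The article gives no sheet length, sentence length or share of difficult words. I use 8 or 10 words per sentence, 2% to 5% difficult words, and 40 to 400 words, for illustration only.

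**Notation.** W = words, S = sentences, D = difficult words.

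- Printed: G = 0.4 × (W/S + D)
- Per 100 words: G* = 0.4 × (W/S + 100 × D/W)

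**Step 1: what the cut-off allows.** G < 6 means W/S + D < 6/0.4 = 15. At 10 words per sentence, D must be below 5, so at most 4 difficult words are allowed in the text scored, whatever its length. At 8 words per sentence the limit is 6.

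**Step 2: where the two versions differ.** Subtracting, G − G* = 0.4 × D × (1 − 100/W). This is zero at W = 100, positive above and negative below. For any non-zero D, the printed score is therefore the stricter one on texts over 100 words and the more lenient one on shorter texts.

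**Step 3: same difficulty, different length.**

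| Words per sentence, share difficult | Version | 50 words | 100 | 200 | 300 | 400 |
|---|---|---|---|---|---|---|
| 10, 4% | printed | 4.8 | 5.6 | 7.2 | 8.8 | 10.4 |
| 10, 4% | per 100 | 5.6 | 5.6 | 5.6 | 5.6 | 5.6 |
| 8, 4% | printed | 4.0 | 4.8 | 6.4 | 8.0 | 9.6 |
| 8, 4% | per 100 | 4.8 | 4.8 | 4.8 | 4.8 | 4.8 |
| 10, 2% | printed | 4.4 | 4.8 | 5.6 | 6.4 | 7.2 |
| 10, 2% | per 100 | 4.8 | 4.8 | 4.8 | 4.8 | 4.8 |

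For example, 300 words at 4% gives D = 12, so G = 0.4 × (10 + 12) = 8.8 and G* = 0.4 × (10 + 4) = 5.6. At 10 words per sentence the printed score reaches 6 when D = 5, that is at 5/0.05 = 100 words for a 5% share, 5/0.04 = 125 words for 4%, and 5/0.02 = 250 words for 2%.

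**Step 4: the lenient direction.** Take 40 words at 10 per sentence with 4 difficult words (10%). G = 0.4 × (10 + 4) = 5.6, a pass. G* = 0.4 × (10 + 10) = 8.0, a fail.

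**Step 5: scoring sentence by sentence.** One 10-word sentence with 4 difficult words (40%) gives G = 0.4 × (10 + 4) = 5.6, a pass. G* = 0.4 × (10 + 40) = 20.0. Sheet length then plays no part, but the rule is at its most lenient.

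**The case against.** The strongest reply is that this is shorthand or a copying slip for an established, cited index, in an article that condenses a fuller protocol. If the team scores samples of about 100 words, count and percentage coincide and the problem disappears. The article does not say what unit is scored, and its wording about revising the sentences could mean sentence-by-sentence scoring. This stands as far as it goes: the documents show a wrongly printed rule, not that any sheet has been or will be mis-scored. It does not clear the rule, because no 100-word sample is stated and the sentence reading makes the count more lenient (Step 5).

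A second reply is that on texts over 100 words the printed rule errs towards strictness, which pushes authors to simplify and serves these readers. That also stands. Undue leniency arises only on texts shorter than 100 words, and no sheet length is given.

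A reader might infer three stronger things, none of which the documents support:

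- **That the score cannot track grade level.** For texts of similar length it still rises with difficulty, and at 100 words it equals the per-100-word version.
- **That this is the only objective safeguard on the sheets.** It is the only numerical criterion given, but the section also requires design to the Simply-Put guide and similar standards, with extensive illustration.
- **That a large, fixed share of the intervention is compromised, for instance that the sheets are half of the health-literacy component.** The article assigns no such weight. The sheets accompany 50-60 minute sessions that open with an animated comic.

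**Conclusion.** The formula is wrong as written. Its score depends on the length of text scored, so a fixed cut-off of 6 does not consistently represent a sixth-grade level. That follows from the printed formula alone, for any non-zero number of difficult words. The size depends on assumed values: at 10 words per sentence and 4% difficult words, equally difficult text scores 5.6, 7.2 and 8.8 at 100, 200 and 300 words. Compared with a per-100-word version, the rule is stricter above 100 words and more lenient below. The factor of 100 cannot be confirmed from the article, because reference [33] is not at hand; the need for a length denominator or a fixed sample length can.

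The consequence is small. It concerns one quality check on the intervention materials. No outcome, sample size or analysis is affected.

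**What to change.** In Section 2.11.1, do one of the following:

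- express the difficult-word term relative to length, for example 0.4 × [(words/sentences) + 100 × (difficult words/words)]; or
- keep the count and state that a sample of 100 words is scored.

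Confirm the chosen form, and that the cut-off of 6 belongs to it, against reference [33]. State the unit scored. Then rescore the fact sheets for the four sessions before they are used and reword any that no longer pass.

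The cost is one corrected line, a recount of a few short texts and perhaps some rewording. No patients, visits or analyses are added.

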### 2.12. Statistical Analysis

Survey data will be coded and analyzed using the Statistical Package for the Social Sciences (SPSS) version 22. In addition to providing descriptive statistics, Chi-square test will be used to compare the distribution of qualitative demographical characteristics between the two groups before intervention. T-test will be used to compare the mean scores of knowledge and health belief model constructs (perceived sensitivity, severity perceived benefits, perceived barriers, and perceived self-efficacy) between the two groups. The Repeated Measure ANOVA analysis will be used to examine and compare changes in the mean scores of knowledge and constructs during the study period in each group and the comparison between the two groups. The post hoc analysis will perform within per groups to compare the times. The Kolmogorov–Smirnov test will be used for checking the normality distribution of the data. The P value of <0.05 will be considered statistically significant.

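### Section 2.12 assigns its outcome tests only to knowledge and the HBM constructs, all secondary, and specifies no test for self-care behaviour, the sole primary outcome

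*Protocol article*

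**What the plan says.** Under the heading "2.9. Primary Outcome Measures" the protocol article has a single entry, Section 2.9.1: "Self-care behaviors will be determined using the 31-item hypertension self-care activity level effects". The Persian version is described there by six domains, with reliability given by domain.

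Knowledge (Section 2.10.1) and the HBM constructs (Section 2.10.2) both stand under the secondary outcome heading.

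Section 2.12 gives each procedure its variables. The chi-square test is for qualitative demographic characteristics before the intervention. For the comparison of arms, "T-test will be used to compare the mean scores of knowledge and health belief model constructs", and the five constructs follow in brackets. The repeated-measures ANOVA is to "examine and compare changes in the mean scores of knowledge and constructs during the study period in each group" and between the groups. The remaining sentences cover software, post hoc comparisons of times within groups, a normality check and the 0.05 threshold. Neither self-care nor the H-scale is mentioned in the section.

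**The concern.** The trial's question is whether the intervention improves self-care; the Discussion makes its next step conditional on that result. A reader who looks in Section 2.12 for the test that answers the question finds named tests for other outcomes only.

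With no specified analysis, the H-scale score, the visit and the test could all be settled after the data are seen. That freedom matters more here because the outcome is self-reported and the patients cannot be fully blinded, both of which the Discussion lists as limitations.

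**Working it through.** The point is textual, so the check is to match every outcome in Sections 2.9 and 2.10 to every test of arms in Section 2.12.

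| Outcome | Status | t-test | Repeated-measures ANOVA |
|---|---|---|---|
| Self-care behaviour (H-scale) | Primary (2.9.1) | not named | not named |
| Knowledge | Secondary (2.10.1) | named | named |
| Perceived susceptibility | Secondary (2.10.2) | named (as sensitivity) | named (as a construct) |
| Perceived severity | Secondary (2.10.2) | named | named (as a construct) |
| Perceived benefits | Secondary (2.10.2) | named | named (as a construct) |
| Perceived barriers | Secondary (2.10.2) | named | named (as a construct) |
| Self-efficacy | Secondary (2.10.2) | named | named (as a construct) |

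Count: 1 + 5 = 6 secondary outcomes with a named test; 0 of 1 primary outcomes.

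*Could the word constructs include self-care?* No. Section 2.12 spells the constructs out, and Section 2.8 lists two separate instruments: "HBM constructs questionnaire (perceived susceptibility, perceived severity, perceived barriers, perceived benefits, and self-efficacy), and self-care behaviors questionnaire".

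*Could another sentence of Section 2.12 reach the H-scale?* The opening sentence says that survey data will be analysed in SPSS, and H-scale data are survey data. It names software, but no test, contrast or visit. The post hoc sentence concerns times within each group, not the comparison of arms.

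*Can the test be inferred from the rest of the article?* No, for three reasons.

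- Score: Section 2.9.1 lists medication adherence, physical activity, low-salt diet, smoking, alcohol and weight management. It defines no total and gives no reliability figure for one.
- Visit: Sections 2.6 and 2.8 give follow-up at 1 and 3 months and rank neither.
- Method: even for the outcomes that are named, Section 2.12 gives both a t-test and a repeated-measures ANOVA and does not say which one decides.

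The score and the visit alone leave 6 domains × 2 visits = 12 possible comparisons at P < 0.05. As an illustration only, suppose that there is no effect on any domain and that the 12 tests are independent. The chance of at least one false positive is then 1 − 0.95^12 = 1 − 0.540 = 0.46. Domains and visits will be correlated, so the true figure would be lower; the documents give no correlations from which to compute it.

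**The case against.** The best case on the other side is that this is an omission in a condensed article. Section 2.12 does not say that only the listed outcomes will be tested, the survey-data sentence could cover the H-scale, and the Discussion plainly expects a self-care result. A fuller protocol or an analysis plan may hold the missing test, and the gap may be a drafting slip. Much of this stands. A reader might infer that the trial will never test self-care; the documents do not show that, only that no test is specified here. It does not dispose of the point, though. Condensation explains missing covariates or model terms. It does not explain a section that twice spells out which outcomes are tested and both times leaves out the main one.

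A reader might also infer that knowledge has replaced self-care as the real endpoint, because Section 2.5 bases the sample size on a knowledge difference. The documents do not support that: the Abstract and Discussion keep self-care as the aim. The basis of the sample size is a separate issue with its own remedy.

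Finally, adding self-care to the two existing test sentences would cure the bare omission, and baseline adjustment is a choice among acceptable methods. That is fair, but such an edit would leave the score and the visit open.

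**Conclusion.** The point holds in this form: the article assigns its tests of arms to six secondary outcomes and specifies none for its only primary outcome. This must be fixed, because the trial's headline claim otherwise has no specified test in the document at hand.

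The conclusion rests on the text of Sections 2.8 to 2.10 and 2.12 and on no numerical figure. The 46% shows how much freedom is left under independence and is not an estimate for this trial. If a fuller document already fixes the self-care analysis, the correction reduces to bringing Section 2.12 into line with it.

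**What to change.** Open Section 2.12 with a primary between-group analysis of self-care that does four things.

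1. **Score.** Define the H-scale score to be analysed. If there is to be no total, name the domains tested and state a multiplicity rule.
2. **Visit.** Fix one primary visit in advance. Three months after the intervention is one option; the sponsor may choose 1 month. The other visit becomes secondary.
3. **Comparison.** Compare intervention with usual care, adjusted for the baseline score, and report a mean difference with 95% CI.
4. **Population.** Analyse patients as randomised, and reconcile this with Section 2.3, which excludes patients who miss more than one class. Only the intervention arm is described as having classes, so that rule could remove patients from one arm after allocation. The text should say whether such patients stay in the analysis.

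Then state that the trial is judged on this result and that knowledge and the HBM constructs are secondary.

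The cost is a few sentences of wording plus two decisions, on the score and on the visit. The self-care questionnaire and the three measurements are already planned, so no new instrument, visit or data collection is needed.

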### 2.5. Sample Size

According to the study performed by Eftekhar Ardebili et al., 2014 [25], the effect size for the study has obtained based on 90% power, 5 % type one error level, and 1 unit difference between the mean score of knowledge before and, after the intervention, 40 patient per group have been estimated. Considering a dropout rate of 10% during the study, we aim to recruit 50 patients per group.

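### Section 2.12 fixes an unadjusted t-test, a repeated-measures ANOVA with an unspecified between-group test, and within-arm post hoc contrasts; one baseline-adjusted between-group comparison should carry the conclusions

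*Protocol article*

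**What the plan says.** Section 2.12 of the protocol article names three analyses for the knowledge and belief scores.

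- A between-group t-test: "T-test will be used to compare the mean scores of knowledge and health belief model constructs". No baseline term and no visit are given.
- A repeated-measures ANOVA of changes in mean scores, "during the study period in each group and the comparison between the two groups". The text does not say whether that comparison is the group main effect or the group-by-time interaction.
- Follow-up contrasts inside each arm: "The post hoc analysis will perform within per groups to compare the times". No between-arm contrast at a follow-up visit is specified after the ANOVA.

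The threshold is stated once: "The P value of <0.05 will be considered statistically significant". Section 2.8 confirms that a baseline exists: "The outcome will be assessed at the baseline, one and 3-month after intervention". Section 2.9 makes self-care behaviour the primary outcome, but section 2.12 attaches none of these tests to it.

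**The concern.** The question in a two-arm randomised trial is how far the arms differ after treatment. Each named method answers it imperfectly.

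- The t-test sets aside a baseline measurement that would reduce residual variance at no cost.
- The ANOVA carries baseline as one of three time levels. At low to moderate correlation this is less efficient than using baseline as a covariate. If the group main effect is the one read, a visit at which the true difference is zero is averaged in.
- The within-arm contrasts do not address the question. Significance in one arm and not in the other is not evidence that the arms differ. Patients cannot be fully blinded (section 2.7) and self-care is self-reported (section 3), so scores may well move over time in both arms and invite that misreading.

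At stake are power at a fixed sample size and the risk that a within-arm result is offered as evidence of benefit.

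**Working it through.** **Inputs from the document.** Section 2.5 gives the error rates, "based on 90% power, 5 % type one error level", the effect, "1 unit difference between the mean score of knowledge before and, after the intervention", and 40 patients per group before the dropout allowance.

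**Assumptions.** The test is two-sided. The correlation r between visits is equal for all pairs and runs from 0.3 to 0.7. The true difference is 1 unit at both follow-ups. No SD is given.

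**The plan's own figure.** The 40 per group cannot be reproduced without an SD. Read as a two-sided, two-sample comparison, it implies

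SD = 1 × √40 / [√2 × (1.960 + 1.282)] = 1.38, a standardised effect of 1/1.38 = 0.72.

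The stated effect is a before-after difference, so this reading is itself an assumption.

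**Power with 40 analysed per group.** In the normal approximation the t-test has a standardised distance of 0.7248 × √(40/2) = 3.24, so power = Φ(3.24 − 1.96) = 0.90.

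- *Baseline-adjusted, one visit.* The variance is multiplied by 1 − r². At r = 0.5, 3.24/√0.75 = 3.74 and power = Φ(1.78) = 0.963.
- *ANOVA group main effect.* The effect is (0 + 1 + 1)/3 = 0.67 units and the variance factor is (1 + 2r)/3. At r = 0.5, 3.24 × 0.667/√0.667 = 2.65 and power = Φ(0.69) = 0.75.
- *ANOVA group-by-time.* Noncentral F with 2 and 156 degrees of freedom; noncentrality = 20 × [(2/3)² + 2 × (1/3)²] / [1.38² × (1 − r)], about 14.0 at r = 0.5.

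| Test | r = 0.3 | r = 0.5 | r = 0.7 |
|---|---|---|---|
| Unadjusted t-test | 0.90 | 0.90 | 0.90 |
| ANOVA group main effect | 0.84 | 0.75 | 0.68 |
| ANOVA group-by-time | 0.81 | 0.92 | 0.99 |
| Baseline-adjusted, one visit | 0.925 | 0.963 | 0.995 |
| Patients per group for 90% power, adjusted (t-test: 40) | 37 | 30 | 21 |

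The gain over group-by-time is about 12 points at r = 0.3, 4 at r = 0.5 and almost none at r = 0.7. With 45 analysed per group (50 recruited less 10%), the gain over the t-test at r = 0.5 is about 5 points: 0.930 to 0.978.

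**Within-arm contrasts.** Suppose both arms truly change by the same amount and each within-arm test has power p. The arms are independent, so P(exactly one significant) = 2p(1 − p). This is 2 × 0.3 × 0.7 = 42% at p = 0.3, 50% at p = 0.5 and 42% at p = 0.7.

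**Missed visits.** A simulation used 4,000 trials per setting, 50 per group and a 1-unit true difference.

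- With about 10% random dropout by month 3, no method showed material bias. At r = 0.3, 0.5 and 0.7 the t-test had power 0.92 to 0.93 and the baseline-adjusted likelihood model 0.94, 0.974 and 0.997.
- With dropout in one arm depending on the 1-month score, bias in the month-3 difference was +0.05 to +0.12 units for the t-test, +0.03 to +0.05 for completer ANCOVA, and about 0 for the likelihood model. The completer change score was also about unbiased in this one scenario.

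**The case against.** The strongest reply is that the plan does contain a between-group comparison of changes over time. A reader might infer that all the planned tests ignore baseline. That does not stand: the ANOVA includes baseline as a time level, and its stated aim of comparing changes fits the group-by-time reading at least as well as the main effect. On that reading the loss is modest at r = 0.5 and negligible at r = 0.7. The dilution to two thirds is therefore conditional on a reading that the text leaves open.

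A reader might also infer that the plan discards patients with a missed visit. The document does not say so. Complete-case deletion follows from conventional repeated-measures ANOVA, not from any stated rule, and it does not apply to a t-test at one visit. Missing-data handling may properly sit in an analysis plan that is not shown, so silence on it is not a fault.

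Nor is the unadjusted comparison biased as such. Under randomisation it is unbiased unless dropout is informative.

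Finally, section 2.12 nowhere states that benefit will be claimed because one arm is significant and the other is not. The 42% to 50% is the chance of a misleading pattern, not the trial's false-positive rate.

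What remains is that the t-test as worded has no baseline term, the ANOVA comparison is unspecified, and the only follow-up contrasts named are within arm. These are choices written into the text, not details left to another document.

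**Conclusion.** The point holds as one of efficiency and clarity, with a real risk of misinterpretation from the within-arm contrasts. Over the t-test, baseline adjustment gains about 2.5 to 9.5 percentage points of power (0.90 to between 0.925 and 0.995). Over group-by-time it gains about 12 points at r = 0.3, falling to almost none at r = 0.7. These sizes rest on an implied SD of 1.38, a two-sided two-sample reading of the sample size, equal correlations of 0.3 to 0.7 and 40 analysed per group. The direction against the t-test holds at any non-zero correlation; the size cannot be settled from the document.

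A claim of lower bias is supported only if dropout depends on observed scores. No such model repairs the exclusion in section 2.3 of patients who miss more than one class, which can remove patients only from the arm offered classes.

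**What to change.** In section 2.12, for each outcome and explicitly for self-care behaviour, name one main analysis: a between-group comparison adjusted for the baseline score. A suitable form is a linear mixed model of the 1- and 3-month scores with fixed effects for group, visit, group × visit and baseline score, and an unstructured covariance. It should include every randomised patient with at least one follow-up score, so that a single missed follow-up does not remove a patient.

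Report the adjusted difference with its 95% CI at one visit named in advance, and rest the conclusion on that. Present within-group changes as descriptive, without significance claims. If the repeated-measures ANOVA is kept as a supporting analysis, state that its between-group test is group-by-time. Address the section 2.3 exclusion separately when defining the analysis population.

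The cost is a few sentences and slightly more modelling work in SPSS, which is already named. No new data, visits or patients are needed.
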